### 2.4. Device and interventions procedures

**Geneactiv wrist-worn actigraphy**: Geneactiv is a watch-like device capturing physical activities with a three-axis accelerometer (Fig 2, left). A light sensor on its surface is capable of detecting ambient illuminance. It’s feasibility and acceptability have been previously validated in dementia populations by ours and other research group independently. Based on our previous results, the team will fit devices, offer manufacturer-approved alternative straps to optimize comfort/appearance, and instruct participants to avoid covering the light sensor.

**Fig 2 pone.0342136.g002:**
[figure not shown]
The two study devices. Left: Geneactiv research-grade actigraphy; right: Re-Timer circadian regulator. (Image taken by the authors.).

**Re-Timer circadian regulator**: Re-Timer is an eyewear emitting 500-nm blue-green visible light with no ultraviolet hazard (Fig 2, right). The device power/irradiance: 506 lux, 230 μW/cm². Theoretically, the light emitted could reduce melatonin secretion and enhance alertness. Prior studies support applicability and safety in adults, those with certain psychiatric conditions, and older adults.

**Device-wearing and assessment schedule** Participants will be retained in the study for 12 weeks (as in Fig 3), during which they will be advised to continue their usual daily routine/care, and will be advised to wear the device for up to 8 weeks, based on the following schedule. On Day 1, baseline demographics and initial assessments (PSQI, NPI-Q, and CBI) will be collected, and the Geneactiv monitoring will start. This is followed by Day 15, where PSQI and NPI-Q are repeated and the Re-Timer intervention begins (daily 30–60 min). On Day 42, assessments including PSQI, NPI-Q, CBI, and a T-QUEST-based semi-structured interview for Re-Timer will be conducted as the blue-green light intervention concludes. Subsequently, on Day 56, PSQI, NPI-Q, and a T-QUEST-based semi-structure interview for Geneactiv will be completed, marking the end of the Geneactiv monitoring period. Finally, a follow-up assessment of PSQI, NPI-Q, and CBI will be performed on Day 84.

**Fig 3 pone.0342136.g003:**
[figure not shown]
Study flow diagram. The study lasts for 12 weeks. Participants will be advised to wear the Geneactiv wrist actigraphy for up to 8 weeks, and the Re‑Timer circadian regulator for up to 4 weeks. They will complete five rounds of assessments on Day 1 (baseline before any device-wearing), Day 15 (baseline before Re-Timer), Day 42 (immediate post-Re-Timer), Day 56 (post-Re-Timer and Geneactiv), and Day 84 (trial completion).

More specifically on the device-wearing:

**Geneactiv**: Days 1–56 (8 weeks) continuous wear. The device is waterproof, but participants may remove the device anytime during the trial if discomfort occurs.**Re-Timer**: Days 15–42 (4 weeks) ≥30 min each time, and up to 60 min/day. The participants will be recommended to wear it twice a day, one in the morning, one in early afternoon, but can remove the device and stop to use at anytime if discomfort occurs. Day-care/hub participants may choose on-site staff-assisted wear and/or home wear. Correct positioning will be taught by the study team members. A participant manual will be provided to record the device-wearing time windows each day and any feedback.

### 2.5 Study registration and ethical considerations

The study has been pre-registered in ClinicalTrials.gov with identifying number: NCT07249918 (URL: https://clinicaltrials.gov/study/NCT07249918). This protocol adheres to the Declaration of Helsinki, and has been approved by the China Medical University and Hospital Research Ethics Committee (CMUH114-REC3–072).

## 3. Outcomes assessments and data analyses

### 3.1. Primary endpoints

**Wear compliance**: Objective Geneactiv wearing time (GGIR-derived); Re-Timer daily wear timing and duration.**Satisfaction (T-QUEST)** at day 42 (Re-Timer) and day 56 (Geneactiv). Between-group differences (patients vs caregivers) will be calculated by independent-samples t-tests.**Qualitative acceptability**: Semi-structured interviews probing convenience, comfort, barriers, and perceived value extended from the T-QUEST will be used. Transcription and thematic analysis with triangulation and independent coder checks will be done.

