### 2.2. Study design and setting

This is a single-arm, dyadic pilot feasibility study lasting 12 weeks, and has started recruitment on 17^th^ November 2025 in CMU Beigang Hospital outpatient psychiatry and neurology clinics, and affiliated dementia day-care center and hubs. Dyads comprise an AD/ mild cognitive impairment (MCI) due-to-AD patient with significant BPSD, and their adult primary caregiver. The recruitment and data collection will be completed in May and August 2026, respectively, while the results are expected to be available in December 2026 (see Fig 1 for the overall timeline).

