#### 2.3.2. Measurements for the primary objectives.

**Taiwanese Version of the Quebec User Evaluation of Satisfaction with Assistive Technology (T-QUEST) [30**]: The T-QUEST will assesses satisfaction with wearables and related services. There are 13 items scored from 1 (very dissatisfied) to 5 (very satisfied), and will be administered to both sides of the dyads at Day 42 (for Re-Timer) and Day 56 (for Geneactiv). If the patient cannot complete the questionnaire, only the caregiver will respond.**Participant Manual:** Each participant will be provided with a personalized manual. The cover will include their name, the study started date, and a QR code for immediate contact with the research team. The manual contains a plain-language introduction to the study’s objectives and tables for participants to record the daily timing and duration of Re-Timer usage and qualitative feedback regarding wearing experience. These subjective records are essential for validating the feasibility of light interventions among dementia patients and their caregivers in rural Taiwan.**Actigraphy Data:** Utilizing the GGIR (an R-based automated package), compliance will be assessed through raw data extracted from the Geneactiv devices. This analysis allows us to calculate precise Geneactiv wearing duration and percentage (Time worn/Total study duration) across the 8-week study period. By examining the distribution of wear time, we can evaluate the long-term acceptability of research-grade wearables in dementia patients and their caregivers in rural Taiwan. These metrics will serve as a primary indicator of whether the protocol is practical for real-world application.**Semi-Structured Interviews:** The interviews will extend from T-QUEST topics to explore participants’ and caregivers’ experiences with both devices, including acceptability, ease of use, comfort, and challenges. Open questions will first be used, followed by iterative, in-depth probing that focuses on convenience, regularity, motivation, and satisfaction. Through this back‑and‑forth process, participants will be encouraged to provide everyday-life examples so that they can fully articulate their experiences and feelings when using the devices. Each interview will last approximately 30–60 minutes in a setting comfortable for participants and caregivers to ensure natural and reliable data collection. Audio recordings will be transcribed and analyzed using thematic analysis to explore perceptions of wearable devices for assessing and managing neuropsychiatric symptoms after trial participation. See supporting information for the interview guide.

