
#### 2.3.3. Measurements for the secondary objectives.

**Pittsburgh Sleep Quality Index (PSQI) [27**]: A questionnaire assesses seven domains related to sleep. Each item scored 0 (no symptom) to 3. PSQI will be administered five times (Day 1, Day 15, Day 42, Day 56, Day 84) to both patients and caregivers. If the patient can complete the questionnaire independently, they will be advised to do so; otherwise, the caregiver will respond on their behalf.**Neuropsychiatric Inventory Questionnaire (NPI-Q) [26**]: Evaluates 12 BPSD symptoms. For each symptom: presence, severity (impact on patient, scored 1–3), and caregiver distress (impact on caregiver, scored 0–5) will be evaluated. It will be administered five times (Day 1, Day 15, Day 42, Day 56, Day 84) by the same primary caregiver throughout the study.**Caregiver Burden Inventory (CBI) [31**]: Assesses caregiver burden with 24 items across five domains (each scored 0–4); higher scores indicate greater burden. It will be administered three times (Day 1, Day 42, Day 84) by the same primary caregiver.

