### 3.3. Sample size and data analysis

As a pilot feasibility study, the sample size is not powered for formal hypothesis testing or clinical efficacy. A convenience sample of 10 patient–caregiver dyads (*N* = 20 participants total) is planned. This sample size is primarily determined by the primary objective of assessing recruitment and retention feasibility. Regarding the secondary exploratory objectives, this sample size is intended to provide sufficient longitudinal data points (via 8-week continuous monitoring) to estimate variance and compute preliminary effect sizes, which will serve as a basis for formal power calculations in future definitive trials.

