**Primary (Feasibility/Acceptability)**: Descriptive summaries of wear‑time compliance and T‑QUEST totals/subscales; between‑group comparisons (patients versus caregivers) via independent‑samples t‑tests as appropriate.**Secondary (Exploratory)**: GGIR extraction of activity, sleep (including sleep regularity index, SRI), and light; mixed‑effects models for longitudinal repeated measures with covariates (age, disease severity, comorbidities). We will evaluate potential dose–response trends between light intensity/duration and BPSD/sleep outcomes. In alignment with the exploratory nature of these endpoints, no formal p-value thresholds for efficacy will be emphasized; instead, we will compute preliminary effect sizes (Cohen’s *d*) and 95% confidence intervals to characterize the data distribution and inform future sample size planning.**Qualitative data analysis**: They will begin concurrently with data collection. Throughout the analytic process, peer debriefing with experienced qualitative researchers will be conducted to critically review emerging codes, categories, and themes, thereby enhancing the credibility and trustworthiness of the findings. The researchers will repeatedly review notes and audio recordings and follow these steps [32,33]:Carefully listen to the recorded interviews and transcribe them verbatim.Read the transcripts repeatedly for a comprehensive understanding, identify meaningful segments, and perform open coding to create a codebook.Apply the concept of the hermeneutic circle [32,34] to interpret experiences related to device use, focusing on aspects such as convenience, regularity, motivation, and satisfaction.Group similar meanings together.Categorize meaningful sentences and commonalities, establish categories, and name them to derive sub-themes.Re-examine the relationship between each interview’s context and the assigned categories for consistency.Reassess the core meaning of the main themes and compile an overall care framework [34].Integrate all content to produce a complete, holistic description

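### The patient–caregiver comparison of T-QUEST scores uses an independent-samples t-test although the two groups are matched dyads, and patients who cannot answer drop out of one side only

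*Protocol article*

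**What the plan says.** The study is dyadic. Section 2.2 states: "Dyads comprise an AD/ mild cognitive impairment (MCI) due-to-AD patient with significant BPSD, and their adult primary caregiver". Section 3.3 gives the size: "A convenience sample of 10 patient–caregiver dyads (*N* = 20 participants total) is planned". Under section 2.3.2 both members of the dyad answer T-QUEST, on Day 42 for Re-Timer and on Day 56 for Geneactiv. The same section adds: "If the patient cannot complete the questionnaire, only the caregiver will respond". The rule for the PSQI in section 2.3.3 is different: if the patient cannot answer, "otherwise, the caregiver will respond on their behalf". T-QUEST has no such proxy wording.

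For the comparison itself, section 3.1 says under T-QUEST satisfaction: "Between-group differences (patients vs caregivers) will be calculated by independent-samples t-tests". Section 3.3 lists descriptive summaries of wear time and T-QUEST, followed by "between‑group comparisons (patients versus caregivers) via independent‑samples t‑tests as appropriate". The mixed-effects models in section 3.3 are listed for the secondary, exploratory outcomes. Section 3.4 says that missing data will be described and their reasons explored at interview.

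**The concern.** An independent-samples t-test takes the variance of the difference in means as the sum of the two group variances. With one patient matched to one caregiver, that holds only if scores within a dyad are uncorrelated. Both members rate the same two devices within one care relationship, so a correlation is plausible. If it is positive, the planned interval is too wide and a real gap in acceptability is more easily missed. If it is negative, the interval is too narrow.

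The second problem does not depend on the correlation. A patient who cannot complete T-QUEST leaves no score, but the caregiver's score stays. The two groups then differ in which dyads they represent as well as in role. If caregivers of patients unable to answer rate the devices differently, that difference enters the contrast and looks like a patient–caregiver gap.

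**Working it through.** **The plan's own figure.** 10 dyads × 2 = 20 participants, which agrees with section 3.3. It is a convenience sample with no power, alpha, effect size or SD, so there is no power calculation to reproduce.

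**Assumptions, none of them in the documents.** SD = 1 in both groups (results are in SD units), bivariate normal scores, two-sided 5% level, within-dyad correlation ρ from −0.3 to 0.7, and m = number of patients who answer.

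**Formulas.** The independent test uses SE = √(1/m + 1/10). The true SE of that difference is √(1/m + 1/10 − 2ρ/10). The paired analysis of m complete dyads has SE = √(2(1 − ρ)/m). Half-widths of the 95% interval multiply the SE by the t quantile on m + 8 degrees of freedom (independent) or m − 1 (paired).

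**All 10 patients answer.** The planned SE is √(2/10) = 0.447 and the planned half-width is 2.101 × 0.447 = 0.94 at every ρ. The true SE is √(2(1 − ρ)/10), for example √(2 × 0.5/10) = 0.316 at ρ = 0.5, and 0.447/0.316 = 1.41. Type I error is from 200,000 simulated trials per value of ρ.

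| ρ | True SE | Planned SE ÷ true SE | Half-width, planned | Half-width, paired | Real type I error of planned test |
|---|---|---|---|---|---|
| −0.3 | 0.510 | 0.88 | 0.94 | 1.15 | 8.2% |
| 0 | 0.447 | 1.00 | 0.94 | 1.01 | 5.0% |
| 0.3 | 0.374 | 1.20 | 0.94 | 0.85 | 2.2% |
| 0.5 | 0.316 | 1.41 | 0.94 | 0.72 | 1.0% |
| 0.7 | 0.245 | 1.83 | 0.94 | 0.55 | 0.2% |

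The paired test stays at 4.9% to 5.1% throughout. Its interval is narrower than the planned one only when ρ exceeds 1 − (2.101/2.262)² ≈ 0.14.

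**Only 6 patients answer (6 against 10).** The planned SE is √(1/6 + 1/10) = 0.516.
- ρ = 0.3: true SE √(0.2667 − 0.06) = 0.455, real type I error 2.9%. Half-widths are 1.11 planned and 1.24 paired.
- ρ = 0.5: true SE √(0.2667 − 0.10) = 0.408, real type I error 1.7%. Half-widths are 1.11 planned and 1.05 paired.

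**Selection.** Let the caregivers of non-answering patients differ by D from the other caregivers, with no patient–caregiver gap within dyads. The mean over all 10 caregivers moves by D × (10 − m)/10. With D = 0.5 SD:
- m = 6: 0.5 × 0.4 = 0.20 SD.
- m = 8: 0.5 × 0.2 = 0.10 SD.

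Restricting the contrast to complete dyads removes this shift.

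**The case against.** The strongest reply is that little depends on this test. Section 3.3 says the sample is not powered for formal hypothesis testing and puts descriptive summaries first. The primary objective in section 2.1 names adherence, satisfaction and practical impact, not a patient–caregiver contrast. Wear time, T-QUEST summaries and interviews are unaffected, and the paired difference can be computed from the same data. This stands, and it limits the severity. It does not make the stated test right for the design.

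Section 3.3 also qualifies the t-tests, as the end of its clause shows. The qualifier names no alternative, however, and section 3.1 carries none.

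A reader might go further than the documents allow in several ways:
- **That the plan inflates false positives.** It does so only under negative correlation. Positive correlation makes the test conservative. Neither sign nor size is documented.
- **That dyads share a home, a helper or wear sessions.** The article does not say so. Section 2.2.1 requires a stable community residence or day-care engagement, and section 2.4 allows staff-assisted wear at the day-care site.
- **That pairing guarantees power.** For a 1 SD gap and 10 complete dyads, planned against paired power is 57% against 66% at ρ = 0.3, but 56% against 52% at ρ = 0. With 6 complete dyads and ρ = 0.3, the paired interval is the wider one.
- **That many patients will be unable to answer.** No expected number is given, and eligibility includes MCI at CDR 0.5. The 6 of 10 above is an illustration.

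Section 3.4 already commits to describing missing data. That informs interpretation but leaves the planned contrast unchanged.

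**Conclusion.** The point holds at moderate severity and should be fixed. The stated test contradicts the dyadic design: its standard error is right only if the within-dyad correlation is zero. With 10 complete dyads it is overstated by 20% to 83% for assumed correlations of 0.3 to 0.7, and understated by about 12% at −0.3. Separately, if some patients cannot answer, the contrast mixes role with dyad selection, by 0.10 to 0.20 SD in the illustrations. Both sizes rest on assumed correlations, SDs, caregiver differences and numbers answering. The case for pairing is a correct error and a like-for-like contrast, not a promised gain in precision. The feasibility conclusions from the descriptive and interview data do not depend on this comparison.

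**What to change.** In sections 3.1 and 3.3, wherever patients are compared with caregivers, replace the independent-samples t-test by the within-dyad difference (patient minus caregiver). Report its mean with a paired-t 95% confidence interval in dyads where both answered, with a Wilcoxon signed-rank analysis as sensitivity.

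A mixed model with a dyad random effect, using all scores, is an acceptable alternative. It keeps the unpaired caregivers, but relies on patient scores being missing at random given the caregiver's score. It should also allow a negative within-dyad covariance.

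In either case, report how many patients could not answer at Day 42 and at Day 56, and show their caregivers' scores separately from those in complete dyads. State that the paired result describes only dyads whose patient can answer.

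The cost is a few sentences of analysis wording, with no new data or participants, and it can be done before the results expected in December 2026. The statistical price is fewer degrees of freedom and, in the paired analysis, loss of the unpaired caregivers. The paired interval is therefore wider at low correlation: 1.01 against 0.94 SD with 10 dyads at ρ = 0, and 1.24 against 1.11 SD with 6 complete dyads at ρ = 0.3.

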### 3.2. Secondary endpoints (exploratory)

BPSD (NPI-Q) and sleep (PSQI) for patients and caregivers across five timepoints (days 1, 15, 42, 56, 84). Caregiver Burden Inventory (CBI) at days 1, 42, and 84.Device-based features: activity metrics; sleep metrics (sleep onset, awakenings, wake time, total sleep time, SRI); light exposure metrics; paired with NPI-Q/PSQI in time-series analyses to explore relationships among light, circadian rhythm, and BPSD.

### 3.3. Sample size and data analysis

As a pilot feasibility study, the sample size is not powered for formal hypothesis testing or clinical efficacy. A convenience sample of 10 patient–caregiver dyads (*N* = 20 participants total) is planned. This sample size is primarily determined by the primary objective of assessing recruitment and retention feasibility. Regarding the secondary exploratory objectives, this sample size is intended to provide sufficient longitudinal data points (via 8-week continuous monitoring) to estimate variance and compute preliminary effect sizes, which will serve as a basis for formal power calculations in future definitive trials.

**Primary (Feasibility/Acceptability)**: Descriptive summaries of wear‑time compliance and T‑QUEST totals/subscales; between‑group comparisons (patients versus caregivers) via independent‑samples t‑tests as appropriate.**Secondary (Exploratory)**: GGIR extraction of activity, sleep (including sleep regularity index, SRI), and light; mixed‑effects models for longitudinal repeated measures with covariates (age, disease severity, comorbidities). We will evaluate potential dose–response trends between light intensity/duration and BPSD/sleep outcomes. In alignment with the exploratory nature of these endpoints, no formal p-value thresholds for efficacy will be emphasized; instead, we will compute preliminary effect sizes (Cohen’s *d*) and 95% confidence intervals to characterize the data distribution and inform future sample size planning.**Qualitative data analysis**: They will begin concurrently with data collection. Throughout the analytic process, peer debriefing with experienced qualitative researchers will be conducted to critically review emerging codes, categories, and themes, thereby enhancing the credibility and trustworthiness of the findings. The researchers will repeatedly review notes and audio recordings and follow these steps [32,33]:Carefully listen to the recorded interviews and transcribe them verbatim.Read the transcripts repeatedly for a comprehensive understanding, identify meaningful segments, and perform open coding to create a codebook.Apply the concept of the hermeneutic circle [32,34] to interpret experiences related to device use, focusing on aspects such as convenience, regularity, motivation, and satisfaction.Group similar meanings together.Categorize meaningful sentences and commonalities, establish categories, and name them to derive sub-themes.Re-examine the relationship between each interview’s context and the assigned categories for consistency.Reassess the core meaning of the main themes and compile an overall care framework [34].Integrate all content to produce a complete, holistic description

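### Patient-versus-caregiver t-tests sit on the primary acceptability outcomes with no lead comparison, while the rule favouring estimates with confidence intervals over p-value thresholds is written only for the secondary endpoints (minor)

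*Protocol article*

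**What the plan says.** Section 3.1 of the protocol article lists three primary endpoints: wear compliance, T-QUEST satisfaction (Re-Timer at day 42, Geneactiv at day 56) and qualitative acceptability. It attaches a test to the T-QUEST entry only: "Between-group differences (patients vs caregivers) will be calculated by independent-samples t-tests".

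The primary analysis paragraph of section 3.3 is broader: "Descriptive summaries of wear‑time compliance and T‑QUEST totals/subscales; between‑group comparisons (patients versus caregivers) via independent‑samples t‑tests as appropriate". Read literally, the tests may reach the subscales and wear time as well as the totals. No comparison is placed ahead of the others.

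On sample size, section 3.3 states: "As a pilot feasibility study, the sample size is not powered for formal hypothesis testing or clinical efficacy". The planned number is "A convenience sample of 10 patient–caregiver dyads".

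The secondary paragraph of section 3.3 says: "In alignment with the exploratory nature of these endpoints, no formal p-value thresholds for efficacy will be emphasized". It then promises Cohen's d and 95% confidence intervals. The endpoints it refers to are the exploratory secondary ones, and its wording is about efficacy.

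Section 2.3.2 adds that where a patient cannot complete the T-QUEST, only the caregiver answers, so fewer than 10 patients may have a score.

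**The concern.** The authors recognised that 10 versus 10 cannot support threshold testing and wrote a suitable remedy, but placed it where it does not reach the primary outcomes. For those outcomes the t-test is the only inferential method described.

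Two misreadings could follow. One of several p-values could fall below 0.05 by chance and be reported as patients and caregivers differing in their acceptance of a device. Conversely, a p-value above 0.05 could be taken to mean that the two groups accept the device equally well, which this sample cannot show. Either would colour the acceptability result, which is part of the study's primary objective (section 2.1).

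**Working it through.** The article gives no alpha, power, effect size or error rate for these comparisons, so there is no stated figure to reproduce. The check asks what the planned tests would do.

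**Inputs from the article**
- Two devices, each with its own T-QUEST occasion (section 3.1).
- 10 patients and 10 caregivers, one caregiver per patient (section 3.3).
- Outcomes: T-QUEST totals and subscales, possibly wear time; independent-samples t-tests (sections 3.1 and 3.3).

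**Assumptions, not in the article**
- Two-sided 0.05 per test.
- Two T-QUEST subscales, of 8 and 5 items (the article gives 13 items in all and no subscale count).
- Normal outcomes and no true difference.
- Correlation between a person's outcomes of 0.3 to 0.7.
- Within-dyad correlation of -0.3 to 0.5.

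**Number of tests**
- Totals only: 2 devices × 1 = 2.
- Totals and subscales: 2 × (1 + 2) = 6.
- With wear time added for each device: 6 + 2 = 8.

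**Upper bound with independent tests**, 1 − 0.95^k:
- k = 2: 9.75%.
- k = 6: 26.5%.
- k = 8: 33.7%.
- Exceeding 50% takes ln 0.5 / ln 0.95 = 13.5, that is 14 independent tests.

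**Effect of the dyads.** With within-dyad correlation ρ, the difference in means has variance 2σ²(1 − ρ)/10, while the unpaired test assumes 2σ²/10. Positive ρ therefore makes the unpaired test conservative and negative ρ makes it liberal. In simulation the error per test is about 5% at ρ = 0, 2.2% at 0.3, 0.9% to 1.0% at 0.5, and 8.3% at −0.3.

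**Chance of at least one p<0.05** (simulation, 40,000 null data sets per setting, each total computed from its two subscales; ranges run over outcome correlations of 0.7 to 0.3):

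| Within-dyad correlation | 2 totals | 6 T-QUEST tests | 8 tests |
|---|---|---|---|
| −0.3 | 13–15% | 21–30% | 26–39% |
| 0 | 8–9% | 14–19% | 17–26% |
| 0.3 | 4% | 7–9% | 9–13% |
| 0.5 | 2% | 3–4% | 4–6% |

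If the subscales and wear time are uncorrelated within a person and the groups are unrelated, the 8-test figure is about 30%.

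**What a single test can show at 10 versus 10**
- Smallest observed |d| with p<0.05: t(0.975, 18) × √(2/10) = 2.101 × 0.447 = 0.94.
- With an assumed 6 patient scores against 10 caregiver scores: 2.145 × √(1/6 + 1/10) = 1.11.
- Power of the unpaired test at ρ = 0: about 19% for d = 0.5 and 40% for d = 0.8.
- At ρ = 0.5: about 12% and 37% (simulation, 200,000 runs).

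Positive dyad correlation thus reduces the risk of a false difference but makes a non-significant result less informative still.

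**Half-width of a paired 95% interval**, in SD units: t(0.975, 9) × √(2(1 − ρ)/10), with t = 2.262.
- ρ = 0: 1.01.
- ρ = 0.3: 0.85.
- ρ = 0.5: 0.72.

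An interval of that width shows directly how little an inclusion of zero would mean.

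**The case against.** The strongest reply is that this is a descriptive pilot. The primary analysis opens with descriptive summaries, the tests are only to be used where appropriate, and the underpowering statement covers the whole study. No alpha is set, and no feasibility or acceptability conclusion depends on a significant difference. Alpha, test order and adjustment commonly sit in an analysis plan that is not shown. All of this stands, and it is why the point is minor and why the absence of a multiplicity procedure is not itself a fault.

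A reader might infer more than the article supports:

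- **That no contrast is named.** Section 3.1 does name patients versus caregivers on the T-QUEST at each device's time point. What is loose is the lead among totals and subscales, and whether wear time is tested: section 3.1 attaches no test to it and section 3.3 can be read either way.
- **That a chance finding is likely.** It is less likely than not in every setting examined. The higher figures require the widest reading of the test list together with unrelated or negatively correlated dyad members.
- **That thresholds will be applied to the primary outcomes.** The no-threshold sentence concerns efficacy, so its absence from the primary paragraph does not prove this. It only leaves the reading of those p-values open.

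What survives is a matter of what the article states, not of what it omits: tests are placed on the primary outcomes, formal testing is disclaimed, and the protective reporting rule is written for the other endpoints.

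**Conclusion.** The point holds as a minor one. Sections 3.1 and 3.3 plan several patient-versus-caregiver t-tests on primary acceptability outcomes without a lead comparison, beside a statement that "the sample size is not powered for formal hypothesis testing or clinical efficacy", and the estimate-and-interval rule does not extend to them.

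Under the assumptions listed, the chance of at least one false difference in 8 tests is about 4% to 26% for within-dyad correlations from 0.5 to 0, and 26% to 39% at −0.3. The article gives no value for that correlation, so the range cannot be narrowed. For the two T-QUEST totals alone it is about 2% to 9% over correlations from 0.5 to 0. The firmer part is the other direction: with only |d| of about 0.94 or more reaching p<0.05, a non-significant comparison cannot support a statement that patients and caregivers accept a device equally.

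**What to change.** In sections 3.1 and 3.3, extend to the primary comparisons the reporting rule already used for the secondary endpoints:

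- Report each patient-caregiver difference (T-QUEST total and subscales for each device, and wear time if it is compared) as a descriptive estimate with a 95% confidence interval computed from within-dyad differences, with the number of complete dyads.
- Use no significance wording.
- State that an interval including zero is not evidence of equal acceptance.
- Say whether wear time is compared between the groups.

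No multiplicity adjustment is needed once the differences are reported this way. The change costs one or two sentences and needs no new data or participants. The small downsides are that individual differences can no longer be called significant, and that a dyad in which the patient has no T-QUEST score drops out of the paired difference, although the caregiver's score still enters the descriptive summary.
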